**Figure 1 Fig1:**
[figure not shown]
**SUCCESS sample size.** Legend: Figure shows the sample size needed (Y axis) to achieve statistical significance with 80% and 90% power, based on varying estimates of attrition (X axis).

#### Recruitment

Three CHWs based at the three clinical sites located in our target communities are leading the recruitment effort. With input from local CABs, field supervisors, and University of Miami study team staff, and using techniques such as community mapping, each CHW devises recruitment strategies that are most appropriate to their locale. Examples include targeting high volume areas such as laundromats, pharmacies, hair salons, flea markets, social service sites (WIC centers), libraries, churches, and community colleges. Other strategies include informing the community about the study through radio stations serving ethnic listeners, free community service advertisings in local newspapers, as well as flyers and posters. Once women are identified through these outreach strategies, the CHWs screen them for potential eligibility. We collect de-identified data from all assessments to track the number of women approached by the CHWs and the proportion who were not study eligible due to reasons such as age or having a Pap smear test within the last 3 years. Among those women who have not had a Pap smear, CHWs ask additional questions addressing the inclusion and exclusion criteria. For those women who are potentially eligible, the CHWs describe the study in further detail. If a woman expressed potential interest, we assign a study ID and collect two contact numbers and follow-up with phone calls to arrange a mutually convenient time and location to conduct an intake interview. CHWs make up to 10 attempts to reach each woman. Ideally, the intake visit takes place within 4 weeks of the initial contact. The CHW and RA complete two appointment reminder calls prior to the visit.

### Methods: data collection, assignment of intervention, and analysis

#### Data collection methods: study intake visit

The study intake visit takes place in an area of mutual agreement with the woman. The intake visit most often occurs in the woman’s home or the local health center but may also take place in other locations. During the intake visit, the RA completes another inclusion screening to verify that the woman meets the study criteria. The study is again explained to the woman and any questions answered. After the woman signs the informed consent form, the RA then proceeds with the structured interview. Based on community input, brevity was the overarching principle driving our study intake procedure. For this reason, we limited the intake survey process to take no more than 30 minutes. In Table 1, we list the questions and instruments used in our intake survey. At the conclusion of the intake visit, the RA thanks the woman for her participation in the study and gives her a study business card and a $25 store gift card to cover their time and effort for participation in the study. The RA tells her to expect a call within a week from the CHW to identify her assigned study group. The RA also reminds the woman that at 6 months there will be a follow-up interview.

**Table 1 Tab1:** **Questions in the SUCCESS intake interview**

Covariates	Questions/Instruments used
Demographics	Age, race/ethnicity, education, income marital status, and citizenship status
Acculturation	Marin-Marin scale [28]
Health literacy	SAHL-S&E [28] (only asked if person are fluent in English or Spanish); not available in Kryeol thus they are only asked if they can read
**Secondary outcomes**	
Access to care (health insurance, having usual source of preventive care, and visit to providers)	Questions from Center for Disease Control National Health Interview Survey Access to Care module
Cervical cancer knowledge, attitudes, and beliefs	Questions from the NCI’s Health Information National Trends Survey (HINTS) [28]

#### Data management

After discussion with some of our community partners and advisory groups, it was felt that collection of data using pen and paper would be more acceptable to the target population than using computer tablets. Thus, we are using paper surveys to collect data which is then input into a Microsoft Access relational study database by a data manager. Initially, all survey entries were double checked for accuracy by a RA and since then every 10^th^ survey is being double checked. Data is also periodically checked by the study statistician for values that are missing, out of range, and for other inconsistencies. As needed, these values are discussed with the study team who then decide how to proceed based on the cause.

#### Allocation and blinding

Once women complete the intake questionnaire they are randomized into one of three possible interventions by the study coordinator who has the pre-generated randomization list from the study statistician. As the study design is hierarchical, with each participant nested within a site, the randomization is based at the site level. A study coordinator notifies the CHW assigned to that woman of the group assignment, and the CHW then follows-up with the women within a week, informing them of their assignment. If women are randomized to Groups 2 or 3, a follow-up visit is scheduled, ideally no later than a month from randomization. The RA who conducts the initial intake visit and 6-month follow-up assessment is blinded to study allocation. However, both women and CHWs are aware of the group to which each participant was randomized.

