#### Confidentiality

To maintain participant confidentiality, study specific ID codes are used in all study tracking and analyses. Only the CHWs and project coordinator have access to the files linking participants with study ID numbers. These password protected files are stored in password protected computers. All paper surveys only have study ID numbers without names. These are stored in locked cabinets in locked offices.

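### The coordinator who assigns each woman also holds the pre-generated list, so the assigner can see upcoming allocations; hold the list elsewhere and audit adherence to it

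*Protocol article*

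**What the plan says.** All places are in the protocol article.

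- **Who assigns (Allocation and blinding).** Women are "randomized into one of three possible interventions by the study coordinator who has the pre-generated randomization list from the study statistician". The list is organised by site: "the randomization is based at the site level".
- **Who passes the result on (same section).** "A study coordinator notifies the CHW assigned to that woman of the group assignment". Allocation is open to those who deliver and receive the intervention: "However, both women and CHWs are aware of the group to which each participant was randomized". The RA who does the intake and the 6-month assessment is stated to be blinded.
- **What comes before assignment (Data collection methods: study intake visit).** The RA re-checks eligibility, obtains consent and completes the interview. On what follows: "The RA tells her to expect a call within a week from the CHW to identify her assigned study group".
- **Study IDs (Recruitment).** They are issued before consent and intake: "If a woman expressed potential interest, we assign a study ID and collect two contact numbers".
- **Accrual (Participant timeline; Trial status).** The target is six women per month at each site. By May 9, 2014, 582 of 600 had been enrolled.

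**The concern.** Allocation concealment requires that nobody who can influence which woman takes the next slot knows what that slot is. Here the person who makes the assignment has the list, so the next group at a site is visible to that person and does not have to be guessed.

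This opens two routes:

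1. **Order of assignment.** If two or more women at one site have completed intake and await assignment, someone who sees the next slots can choose who takes which.
2. **Foreknowledge among recruiters.** A study coordinator is in contact with the CHWs about assignments. If a CHW learned the next group at her site, she could let it influence whom she schedules for intake next, and when.

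The outcome would be sensitive to either. Screening is self-reported, and women lost to follow-up are counted as unscreened. A woman's willingness to be screened and the ease of reaching her therefore both affect her recorded result. Blinding the RA protects outcome assessment, and intention-to-treat analysis preserves the arms as assigned. Neither corrects arms that already differed because of how women were matched to slots.

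**Working it through.** The plan gives no figure on this point to reproduce. The check is a reading of the procedure, followed by simple arithmetic on how often there would be any order to choose.

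**Step 1: what the sequence protects.** Assignment follows intake: "Once women complete the intake questionnaire they are randomized into one of three possible interventions". By then the woman has consented and a blinded RA has confirmed eligibility, so an assigner who sees the list cannot use it to admit or refuse her. What is left open is her position relative to other women at the same site who have also finished intake.

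**Step 2: whether study IDs could show the order.** IDs are given at first interest, before the intake visit. ID order is therefore not intake order, and it cannot by itself show that the list was followed.

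**Step 3: how often women would be pending together.** Assume Poisson arrivals at one site at the stated six per month, which is 6 × 12 = 72 per year. The share of women who have at least one other same-site intake in the same interval is 1 − exp(−λ), where λ is the expected number of intakes per interval.

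| Interval between intake and assignment | λ | 1 − exp(−λ) |
|---|---|---|
| Same calendar day | 72/365 = 0.197 | 0.18 |
| Same working day (260 per year) | 72/260 = 0.277 | 0.24 |
| Same week | 72/52 = 1.385 | 0.75 |

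The other accrual figures in Participant timeline change this little. Two hundred women over 40 months is 5 per month, which gives 15%, 21% and 68%. Twenty per month over three sites is 6.67 per site, which gives 20%, 26% and 78%.

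**Step 4: which row applies.** The article does not give the interval between intake and assignment. The one-week period it mentions is the time for the CHW to call the woman with her group. It does not describe a week in which unassigned women accumulate. The rows are therefore a range of possibilities and do not estimate what happened.

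**Step 5: reach of a change now.** 600 − 582 = 18 women remained to be enrolled at the stated date.

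**The case against.** The strongest reply is that recruitment, consent, eligibility and intake are separated from assignment, that a blinded RA does the last three, and that the text gives the coordinator no contact with women before assignment. The coordinator may therefore know little on which to select. This stands. It narrows the concern to the order of assignment and to disclosure to CHWs, and it is a reason not to put a size on the bias.

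A second reply is that a condensed article may leave concealment steps to the full protocol. That is fair for detail the article omits. The point rests on what the article states, namely that the assigner has the list. That the whole list is visible is an inference, but it is the ordinary meaning of the sentence, and nothing suggests release one line at a time.

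A reader might infer more than the text supports:

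- **A bias of several percentage points per contrast.** That would require weekly batching, an assumed share of more motivated women, an assumed gap in their screening rates, an assigner who knows who they are, and a fixed preference among the three groups. The document gives none of these.
- **A bias that must favour the CHW arms.** Someone wishing to help could equally send the hardest-to-reach women to navigation, which would pull the contrasts toward the null.
- **One coordinator who also holds the names.** Confidentiality says "Only the CHWs and project coordinator have access to the files linking participants with study ID numbers", but Allocation and blinding speaks of a study coordinator, and nowhere are the two equated. The point does not need this, because whoever assigns must already know which woman and which CHW are concerned.
- **That adherence to the list can no longer be shown.** The statistician produced the list and may well still have it, so an audit should be possible.

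**Conclusion.** The weakness is real and comes from the stated procedure: the assigner can see upcoming allocations in a trial where the CHWs know each woman's group. It concerns which pending woman takes which slot, and whether upcoming groups could reach the recruiters. It does not concern consent, eligibility or blinded outcome assessment.

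Neither the size nor the direction of any bias can be determined from the document. The opportunity would touch about 18 to 24% of women under same-day assignment and about 75% under weekly batching, assuming Poisson arrivals at six per month per site. How far an opportunity becomes bias depends on what the assigner knows, which is not stated. Nothing in the document suggests misuse. With 582 of 600 women enrolled, the main value now lies in checking that the list was followed.

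**What to change.** **Remaining women (about 18).** In Allocation and blinding, state that the study statistician keeps the site lists. After each completed intake the coordinator registers the study ID, the site, and the date and time of completion. The statistician then returns one assignment, in order of intake completion within site. The coordinator does not see later slots.

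**Women already allocated.** Where intake dates are recorded, the statistician compares each assigned arm with the original site list in intake order and reports the number of departures. A single skipped slot displaces every later one, so breaks in sequence should be reported as well as mismatched women. If there are departures, repeat the primary analysis by list-dictated arm as a sensitivity analysis, leaving the primary analysis as planned.

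**Limits of the audit.** If only dates are available, women who finished intake at one site on the same day cannot be ordered, so swaps within a day would not show. The audit also cannot detect foreknowledge among the CHWs. The report should state both limits.

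**Cost.** One short message per remaining woman, possibly with a brief delay before the CHW's call, and a one-off comparison of existing records. No new staff or system is needed.

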#### Follow-up evaluation at 6-months

At 6 months, a RA blinded to study group allocation does a 6-month follow-up evaluation. The visit takes place in an area of mutual agreement with the woman. Up to 10 phone calls are made to the patient at different times and days, including weekends, to try to contact them to schedule the appointment. If the participant cannot be reached, attempts will be made using the other contact information that was provided during study intake or follow-up phone calls. If after 2 months the RA has been unable to schedule the appointment, in most cases, participants will be considered as lost to follow-up. However, in some cases the interval may be extended. This may occur if, for example, a participant was out of the country for a few months but had planned to return.

#### Statistical analysis

All data will be analyzed using the intent-to-treat principle and we assume that women who were lost to 6-month follow-up did not have any screening. Initially, we will perform an explanatory data analysis; visually via graphics/plots, such as scatter and box-whisker plots, and numerically by descriptive statistics, such as range, median, means, and standard deviations, for measurements taken on a continuous scale. Percentages and various types of cross-tabulations will be performed for measurements taken on a categorical scale. Corresponding confidence intervals for means and proportions will also be calculated. To have a better understanding of the relationships among different study measurements, parametric or non-parametric correlation coefficients, bivariate, and multidimensional cross-tabulations, scatter, and box-whisker plots will be constructed. Prior to analyses, baseline differences of key covariates from each arm will be examined with respect to our primary outcome, particularly those related to socio-economic status. We will also examine differences on key variables between participants who completed the study and lost-to-follow-up. Analysis of variance for differences in means and *χ*^2^ test for difference in proportions will be used to test the differences among the three study arms. Several univariate and multivariate logistic regression models will be used to calculate odds ratios and corresponding 95% confidence intervals for exploring the result of having had Pap smear screening and the relationship to various types of key study covariates. Two-way interaction terms between various study variables and the study arms will also be included in the models. Standard diagnostic tools will be used to assess model fit. Transformations of the continuous data in order to meet statistical assumptions will be undertaken when indicated. We will treat primary and secondary outcomes as separate clusters, setting a 0.05 level of significance to the primary outcome. A Bonferroni correction will be applied to secondary outcomes. All statistical analyses will be carried out using SAS® version 9.3 or later for Windows (Cary, NC, US) and/or the R project for Statistical Computing for Windows (http://www.r-project.org/).

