#### Sample size

In the study, we are recruiting 600 women from three study sites. The sample size was chosen to detect effects associated with a 20 point increase in the proportion of women screened in Group 2 (CHW) versus Group 1 (outreach) and an additional 15 percentage point increase in Group 3 (HPV self-sampling) versus Group 2. In addition, as women are randomized within each site, sample size calculations were adjusted to account for clustering of patients within each community. Based on these parameters, we examined power estimates under a variety of assumptions for attrition with estimates ranging from 0% to 30%. As shown in Figure 1, with a total sample size of 600 women (200 women in community), we will have sufficient power for the main study hypotheses, under a variety of attrition rate assumptions at a 0.05 level of significance.

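### The only between-arm test named for proportions is a three-arm chi-square at one 0.05 level; it settles neither of the two contrasts the trial was sized for and leaves out site

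*Protocol article*

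**What the plan says.** The Statistical analysis section pairs analysis of variance for means with a chi-square "test for difference in proportions will be used to test the differences among the three study arms" for proportions. Its multiplicity rule separates primary from secondary outcomes, "setting a 0.05 level of significance to the primary outcome" and applying Bonferroni to the secondary ones. It names no pairwise comparison for the primary outcome, no order or split of the 0.05, and no site term. Logistic models are mentioned, but as exploratory.

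The Sample size section states two effects: a 20-point gain for Group 2 over Group 1, and "an additional 15 percentage point increase in Group 3 (HPV self-sampling) versus Group 2". It claims sufficient power for the main hypotheses "under a variety of attrition rate assumptions at a 0.05 level of significance". It says women are randomised within each site and that "sample size calculations were adjusted to account for clustering of patients within each community". The Allocation and blinding section calls the design hierarchical, "with each participant nested within a site, the randomization is based at the site level". In the planned analyses, community appears explicitly only under Subgroup analysis, which is labelled hypothesis-generating.

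**The concern.** The trial asks two questions: does navigation by a community health worker beat brochures, and does adding a self-sampling option beat navigation alone? The Background and Objectives sections make the self-sampling strategy the centre of the study. A three-arm chi-square asks only whether the arms are all alike. If navigation works, that test will almost certainly be significant whether or not self-sampling adds anything.

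The alternative is to run the two sized comparisons separately. The document then does not say how one 0.05 covers two hypotheses. Either the test misses the hypotheses, or the stated error level is not held.

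Site is a lesser matter. Allocation is made within site and the sizing takes account of community, but the named test ignores it.

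**Working it through.** **Inputs.** From the document: 600 women, 200 per community; differences of 20 and 15 points; level 0.05; randomisation within site. Not given, so assumed: 1:1:1 allocation (200 per arm), two-sided tests, a Group 1 rate of 10% to 40% (20% to 40% in step 2), and the site rates in step 5.

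**1. The plan's own figure.** The 600 cannot be reproduced, because the Group 1 rate, the clustering adjustment and the allocation ratio are not stated and the figure is not shown. It can be checked for plausibility with

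n per arm = [1.96·√(2p̄(1−p̄)) + 0.8416·√(p₂(1−p₂)+p₃(1−p₃))]² / (p₃−p₂)².

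For a Group 1 rate of 20%, p₂ = 0.40, p₃ = 0.55 and p̄ = 0.475. Then n = (1.384 + 0.588)²/0.0225 ≈ 173 per arm, or 519 in total for 80% power without attrition. Over Group 1 rates of 10% to 40% the total is 456 to 519 for 80% power and 609 to 693 for 90%. So 600 is in the region that the Group 3 versus 2 contrast needs. The three-arm test at the design rates has power above 99.9% even with 140 per arm, so it is not what drives the sample size.

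**2. Three-arm test when self-sampling adds nothing.** Set Group 3 = Group 2 = Group 1 + 0.20. The noncentrality is λ = n·Σ(pᵢ−p̄)²/[p̄(1−p̄)] on 2 df, with critical value 5.991. The sum of squares is (0.1333² + 2·0.0667²) = 0.02667 in every row.

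| Group 1 rate | p̄ | λ at n = 200 | Rejects | Rejects at n = 140 |
|---|---|---|---|---|
| 20% | 0.333 | 24.0 | 99.5% | 96.5% |
| 30% | 0.433 | 21.7 | 99.1% | 94.7% |
| 40% | 0.533 | 21.4 | 99.0% | 94.4% |

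The n = 140 column is only a smaller-sample check. The plan counts lost women as unscreened, so they stay in the denominator.

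**3. Ungated contrasts at 0.05 each.** Two independent tests would give 1 − 0.95² = 9.75%. The two contrasts share Group 2, so their statistics correlate at −0.5 with equal arms. Simulation (2 million draws) gives 9.1%, and 12.2% if all three pairs are tested.

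**4. Gated procedure.** If both contrast nulls hold, all three arms are equal, and that is the hypothesis the 2-df test examines at 0.05. If only one null holds, its own 0.05 test bounds the error. The procedure is therefore closed and holds 0.05 familywise. Simulated error under the global null for the two contrasts is 4.2%. At the design rates the gate almost always opens: power for Group 3 versus 2 at 200 per arm is 85% to 90% with or without it (Group 1 rate 10% to 40%). Bonferroni at 0.025 would give 78% to 84%.

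**5. Omitting site.** Simulation, 40,000 runs, 67 women per arm in each of three sites, plain chi-square against a Cochran-Mantel-Haenszel (CMH) test:

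| Assumed site rates | 2-df null rejection, plain / CMH | Power, Group 3 vs 2, plain / CMH |
|---|---|---|
| 30/30/30% | 4.9% / 4.9% | 86.4% / 86.3% |
| 20/30/40% | 4.3% / 4.8% | 86.5% / 87.1% |
| 15/30/45% | 3.9% / 5.0% | 87.0% / 88.6% |
| 10/30/50% | 3.2% / 5.0% | 87.6% / 89.9% |

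Leaving site out never raises the error rate here. It costs about 0 to 2.4 points of power.

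**The case against.** The document never calls the chi-square its primary test. The sentence is a general one, follows remarks on baseline and dropout comparisons, and does not rule out pairwise chi-squares. The logistic models could also yield arm-specific odds ratios and might include site. A condensed article commonly leaves the order of contrasts to a fuller plan. All of that is fair, which is why the point is limited to the only between-arm test named. What remains is a mismatch inside the document: it fixes a test and an error rule for the primary outcome, and neither refers to the two hypotheses that its own sample size names.

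The two error calculations also belong to different readings. One three-arm test at 0.05 has 5% error and no multiplicity problem; the 9% arises only if the contrasts are tested separately without a gate, which the document does not say it will do. Nor is the three-arm test itself the fault, since the remedy starts with it. What is missing is the step after it.

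Three stronger readings are tempting and not supported:

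- **Omitting site invalidates the test.** It makes the test at most mildly conservative, and that depends on sites differing and on balanced allocation within site. The document mentions a pre-generated list but no blocking; under simple randomisation with a common ratio the pooled test keeps its level.
- **Interaction terms distort the arm effect.** The document says "Two-way interaction terms between various study variables and the study arms will also be included in the models", but these models are described as exploratory and nothing makes them the source of the primary comparison.
- **The clustering wording should become stratification.** That text reports how the calculation was done. Rewording it without redoing the calculation would misreport it, and the size of the adjustment is not given.

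**Conclusion.** The point stands in limited form. The named test does not answer the self-sampling hypothesis: with 200 per arm and a Group 1 rate of 20% to 40%, it rejects about 99% of the time when Group 3 is no better than Group 2, provided Group 2 is 20 points above Group 1. Separate ungated tests would carry about 9% familywise error against the stated 0.05. These figures rest on 1:1:1 allocation and assumed Group 1 rates, but the conclusion does not change over the range tried.

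The site term is a secondary improvement that brings the analysis into line with the randomisation. Its benefit is small and rests on assumed site rates.

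The arms, data and sample size can support both contrasts, so this is a wording gap worth closing before analysis, not a defect that threatens the trial.

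**What to change.** In the Statistical analysis section, state the primary analysis as follows:

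- Compare the arms with stratification by site, using either a CMH test or logistic regression with arm and site as fixed effects.
- Test the 2-df arm effect at two-sided 0.05. Only if it is significant, test Group 2 versus Group 1 and Group 3 versus Group 2, each at 0.05.
- Report site-adjusted risk differences with 95% confidence intervals for both contrasts, since the sample size is stated in percentage points.

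Leave the exploratory models and the sample-size text as they are. The cost is a few sentences. Each woman's site is known from the within-site randomisation, no further women or data are needed, and power for Group 3 versus 2 is essentially unchanged by the gate. The Trial status section reports 582 of 600 women enrolled on May 9, 2014, so the wording should be fixed and dated before the final comparison is run.

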#### Secondary outcomes

There will be two secondary outcomes. The first is cervical cancer knowledge. Women in Groups 2 and 3 receive a 1-hour health education session. Thus, changes in cervical cancer knowledge from baseline to follow-up will be compared across the three groups. For each woman, the change in proportion of questions answered correctly will be examined.

The other secondary outcome will be access to care. Although improving access to care is not specifically part of the intervention, conceptually, a major role for CHWs is linking women in their communities to health care. Thus, as a secondary outcome we will determine the impact of our CHW intervention at improving access to healthcare. This will include an analysis of survey questions regarding having health insurance, a usual source of preventive care, and number of visits to a provider within the last year. By including this as a secondary outcome, it will help us examine whether access to care improved among participants having a CHW. This data will also help to address concerns that women in Group 3 who receive negative results from their completed HPV may believe that they are healthy and do not need to see a health care provider. That is, it will allow us to examine whether access among participants in Group 3 remained the same as those in Group 2.

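### Plain Bonferroni on the secondary outcomes gives up power on access to care; Holm's step-down on the same p-values holds the same family-wise error and never rejects less

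*Protocol article*

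**What the plan says.** The Statistical analysis section of the protocol article separates the families ("We will treat primary and secondary outcomes as separate clusters"), gives the primary its level ("setting a 0.05 level of significance to the primary outcome"), and then fixes the method for the rest: "A Bonferroni correction will be applied to secondary outcomes". It names no step-down or other sequential rule, so single-step Bonferroni is the ordinary reading. It states neither the family level for the secondary outcomes nor the divisor.

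The Secondary outcomes section says "There will be two secondary outcomes": knowledge and access to care. On knowledge it notes that "Women in Groups 2 and 3 receive a 1-hour health education session"; under the Group 1 intervention, women receive brochures. Access is to be analysed through survey items on "having health insurance, a usual source of preventive care, and number of visits to a provider within the last year". Access is also meant to show whether "access among participants in Group 3 remained the same as those in Group 2".

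Analysis of variance and chi-square tests "will be used to test the differences among the three study arms", so each outcome or item yields an ordinary p-value. Confidence intervals for means and proportions are planned, but no simultaneous or Bonferroni-adjusted intervals are mentioned. No unequal weights and no other reason for single-step testing are given.

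**The concern.** Single-step Bonferroni holds each of m secondary tests at the family level divided by m, whatever the other tests show. Holm's procedure orders the same p-values and compares the smallest with α/m, the next with α/(m−1), and so on, stopping at the first failure. It controls the family-wise error strongly at α under any dependence. Its first step is the Bonferroni threshold and every later step is more lenient, so it cannot reject less.

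The two outcomes here differ in how easily they should move. Knowledge is what the one-to-one session teaches. Access is a downstream effect that the article says is not specifically part of the intervention, and the Sample size section sizes the trial only on the proportion screened. Access is nevertheless the outcome meant to show whether community health workers (CHWs) link women to care, and whether women with a negative self-sample stop seeing providers. A real difference in access could be declared non-significant solely because of the procedure chosen.

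**Working it through.** **Inputs.**
- From the article: two secondary outcomes; three access items; 600 women in three arms; attrition considered up to 30%.
- Assumed: family level 0.05 two-sided for the secondary outcomes; equal allocation, hence 600/3 = 200 per arm; m = 2 (one test per outcome) or m = 4 (knowledge plus three access items); all secondary effect sizes.

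The article gives no power or adjusted level for the secondary outcomes, so there is no figure of its own to reproduce.

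**1. Thresholds.**

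| Tests | Bonferroni, every test | Holm, successive steps |
|---|---|---|
| m = 2 | 0.025 | 0.025, 0.05 |
| m = 4 | 0.0125 | 0.0125, 0.0167, 0.025, 0.05 |

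**2. Power for access once knowledge is rejected, m = 2.** If power is P at level a₀, the standardised effect is z_P + z(1−a₀/2), and power at level a is Φ(z_P + z(1−a₀/2) − z(1−a/2)). Here z(0.9875) = 2.241 and z(0.975) = 1.960. For P = 80%: Φ(0.842 + 2.241 − 1.960) = Φ(1.123) = 87%.

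| Power at 0.025 | Power at 0.05 |
|---|---|
| 50% | 61% |
| 60% | 70% |
| 70% | 79% |
| 80% | 87% |

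**3. The same on a proportion scale.** One pairwise contrast in an access item, with assumed rates. Power = Φ(Δ/SE − z(1−a/2)), SE = √[(p₁q₁ + p₂q₂)/n].
- 50% v 62%, n = 200: SE = √[(0.2500 + 0.2356)/200] = 0.0493, Δ/SE = 2.435. Power is Φ(0.194) = 58% at 0.025 and Φ(0.475) = 68% at 0.05.
- 50% v 65%, n = 200: SE = 0.0489, Δ/SE = 3.070. Power is 80% and 87%.
- 50% v 65%, n = 200 × 0.7 = 140: SE = 0.0584, Δ/SE = 2.568. Power is 63% and 73%.

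**4. Four tests.** An access item with 80% power at 0.0125 (z = 2.498) has 83%, 86% and 92% at 0.0167, 0.025 and 0.05. Those levels apply after one, two and three other rejections respectively, so 92% needs all three other tests rejected first.

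**5. Unconditional comparison.** Steps 2 to 4 condition on earlier rejections. To remove that condition, both procedures were applied to the same simulated two-sided p-values (400,000 replicates, correlation 0 or 0.3). The first column gives power at an unadjusted 0.05. Results are for independent tests.

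| Scenario | Bonferroni, access | Holm, access |
|---|---|---|
| m = 2, knowledge 99%, access 80% | 71% | 80% |
| m = 2, knowledge 80%, access 80% | 71% | 78% |
| m = 2, knowledge 90%, access 50% | 39% | 48% |
| m = 2, knowledge null, access 80% | 71% | 71% |
| m = 4, knowledge 99%, all three items 80% | 62% | 75% |
| m = 4, knowledge 99%, one item 80%, others null | 62% | 66% |
| m = 4, knowledge null, one item 80%, others null | 62% | 62% |

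At correlation 0.3 the second row's Holm figure becomes 77% and the fifth row's 74%; the others barely move. In every replicate each Bonferroni rejection was also a Holm rejection. With all hypotheses null, the family-wise error was identical for the two methods: 0.050 (m = 2) and 0.049 (m = 4) when independent, 0.049 and 0.047 at correlation 0.3.

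**The case against.** The strongest reply is that nothing here is an error. Bonferroni is valid, prespecified, conservative and simple, and preferring a sharper method may be a matter of taste. It is true that no type I error is at stake. But this is not a trade-off between two defensible properties. Bonferroni's usual compensation is simple matching simultaneous intervals, and the article plans none.

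Second, the article does not say single-step, and the divisor and family level may sit in an analysis plan not shown. That stands as a limit on the power figures: the 0.025 level is an assumption that needs m = 2 and a family level of 0.05. It does not affect the ordering of the two methods, which holds for any m and any level.

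Third, the gain is conditional. That also stands: it appears only if another secondary outcome is rejected first, and is essentially zero if knowledge is unaffected and no other access item is rejected. The article gives no effect size for knowledge; that it is the likely first rejection is a judgement from the contrast between session and brochure. Equally, if access had the smaller p-value, the gain would go to knowledge.

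Fourth, Holm does not establish that access in Groups 2 and 3 is the same. Correct: a non-significant result is not evidence of sameness under either method. Greater power only makes a real difference less likely to be missed.

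Finally, the article reports 582 of 600 women enrolled, six-monthly interim analyses of the primary outcome, and preliminary tables available to the team on request. A late move to a more lenient rule therefore needs a dated amendment. That bears on how the change is made, not on whether it is an improvement.

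**Conclusion.** The concern holds as an avoidable loss of efficiency, not as an error in type I control. Holm's procedure dominates the stated correction at the same family-wise level, and the article gives nothing in return for the loss. That conclusion rests on no assumed effect size, only on reading the stated correction as single-step.

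The size does rest on assumptions: family level 0.05, m = 2 or 4, and hypothetical effects. For access with 80% power at an unadjusted 0.05, the loss is about 9 points with two tests (71% against 80%) when knowledge is strongly affected. It is about 13 points with four tests (62% against 75%) when all three access items are affected as well, and nil when no other secondary outcome is rejected. The primary outcome and its 0.05 level are untouched. The change should be made, but the validity of the trial does not depend on it.

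**What to change.** In Statistical analysis, replace the Bonferroni sentence with: *Secondary outcomes will be tested with Holm's step-down procedure at a family-wise level of 0.05.* Report Holm-adjusted p-values. The confidence intervals can stay as planned.

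The cost is one sentence, documented as an amendment dated before any secondary outcome is compared by arm. It needs no new data, no change in conduct and no extra type I error. The one thing given up is simple matching simultaneous confidence intervals, which the article does not promise.
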